## Abstract

**Background:**

Online gambling has been legalized in France in 2010. Licenses are issued to gambling operators who demonstrate their ability to respect the legal framework (security, taxation, consumer protection, etc.). The preventive measures to protect vulnerable gamblers include an obligation to provide online gambling moderators. These moderators should allow gamblers to limit their bets, exclude themselves from the website for 7 days, and consult the balance of the gambler’s account at any time. However, there are only a few published reports of empirical research investigating the effectiveness of Internet-based protective measures implemented by French law. Moreover, no empirical research has yet studied the impact of bonuses on gambling behaviors.

**Methods/Design:**

This research is an experimental randomized controlled trial, risk prevention targeted. The research is divided into four sub-studies depending on the studied moderator: limiting bonuses, self-exclusion, self-limitation and information. The study sample consists of 485 volunteers. For each experimental condition and the control groups, the sample is composed of gamblers equally recruited from gamblers having preferences in each of the three major forms of games (lottery and scratch tickets, sports and horserace betting, and poker). For each form of gambling, the gamblers are recruited in order to obtain as many problem gamblers as non-problem gamblers. According to the randomization, the experimental session begins. The experimental session is a gambling situation on a computer in our research center. The gambler is invited to play on his favorite gambling site as usual, with his own gambler account and his own money. Data collected comprise sociodemographic characteristics, gambling habits, an interview about enjoyment and feeling out of control during the gambling session, moderator impact on gambling practice, statement of gambling parameters and questionnaires (BMIS, GRCS, CPGI, GACS). Moderator efficiency is assessed based on the two major characteristics of gambling behavior: money wagered and time spent in gambling.

**Discussion:**

The results of this research will be important to prevent online problem gambling and influence policy-makers.

**Trial registration number:**

NCT01789580. Registered 8 February 2013

## Background

If the majority of gamblers maintain a recreational and controlled practice, some of them will develop an excessive practice. Gambling disorder is defined in the Diagnostic and Statistical Manual of Mental Disorders, Fifth Edition (DSM-V) as a persistent and recurrent problematic gambling behaviour leading to clinically significant impairment or distress [1]. The first French prevalence study conducted in 2010 showed that 1.3 % of adults in the general population were problem gamblers [2]. By focusing solely on gamblers during the year, a proportion of 2.8 % of problem gamblers was found. Another study conducted in 2013 among online gamblers showed a prevalence of problem gambling for 17 % [3]. These figures are higher than those observed with traditional games.

Several features can explain the fact that online gambling is more addictive compared with offline gambling [4]. Game availability and accessibility are certainly the most important risk factors on the Internet. A gambler can access an almost unlimited supply of games on the Internet from home, 7 days a week and 24 h a day. Moreover, online gambling lets you gamble on multiple sites at once, thus increasing gambling frequency and decreasing the time between setting and gain. This promotes loss of control in gamblers. The particular method of payment related to Internet support (use of a credit card) can also promote a loss of awareness of financial losses. Anonymity is also part of the same phenomenon. Many players prefer to play online because they feel no judgment about their gambling behavior contrary to what they may experience in real places where they can be identified as patrons or “big” players. This contributes to disinhibition phenomenon [5] of gambling practice, as well as the comfort brought by online practice (no need to prepare to go out, can play everywhere, can associate with the consumption of alcohol or drugs …). Finally, some commercial techniques facilitate online gambling as bonuses. Bonuses are amounts of money deposited by gambling operators in gambling accounts at the time of registration (acquisition bonus) or later (retention bonus). They represent about 50 % of the marketing budget for gambling operators or about 62 million euros in 2013 [6].

In France, the Regulatory Authority for Online Gambling (ARJEL) is the administrative authority that oversees the application of the law and issues licenses to gambling operators who have demonstrated their ability to respect the legal framework (security, taxation, consumer protection, etc.). The preventive measures to protect vulnerable gamblers include an obligation to provide online gambling moderators. These moderators should allow gamblers to limit their bets, exclude themselves from the website for 7 days, and consult the instant balance of the gambler's account at any time. However, with no precise specification for implementing these moderators, gambling operators, who have mainly commercial interests, often provide minimum protection for gamblers.

Furthermore, there are only a few published empirical research studies investigating the effectiveness of Internet-based protection implemented by the ARJEL. So we also opted to consider relevant research pertaining to the effectiveness of land-based protection.

About self-exclusion, Ladouceur and his colleagues [7] found that the majority of self-excluders at land-based venues had significantly more control over their gambling behavior, and reported positive effects on their life (mood, social and family life, work). Similar findings were reported in others research work [8–10]. To our knowledge, no study evaluates the effectiveness of self-exclusion on Internet gambling.

The effectiveness of self-limitation on money spent was studied on the Internet, but only for sports betting. Nelson and his colleagues [11] demonstrated that self-limitation programs appear to be promising options for Internet gamblers at risk for gambling problems, but very few used them . Self-limitation appears to help gamblers reduce their betting activity (frequency of betting, bets per day, and total wagered). Time spent in gambling, not just money spent, appears to be an important indicator of gambling problems, according to the type of games, but that was not studied.

Concerning information about gambling risks, Monaghan and Blaszczynski [12] indicate that pop-up messages may be an appropriate mode of presentation for harm-minimization signs on Electronic Gaming Machines (EGMs). The study demonstrates that self-appraisal messages had the greatest reported impact on a gambler’s thoughts and behavior. At present, information for harm-minimization does not exist in Internet gambling. Finally, no empirical research has studied the impact of bonuses on gambling behavior.

In the light of the specific addictive characteristics of online gambling, it is essential to evaluate the effectiveness of existing means of protection and propose new ones in order to improve responsible gambling measures specific to online gambling and thus protect the most vulnerable gamblers.

The main objective is to assess the effectiveness of four types of gambling moderators: limiting bonuses, self-exclusion, self-limitation and information. Some of them are already proposed by law, but not evaluated, and others are not yet available.

The efficiency of the moderators is assessed depending on gambling type (games of chance without skill, such as lottery or scratch tickets, semi-skilled games of chance such as sports betting or horserace betting, and skilled games of chance such as poker [13]) and gambler status (problem gambler or no problem gambler), and based on the two major characteristics of gambling behavior: money wagered and time spent in gambling. The aim is to provide a system of protection based on the type of game and the status of the player.

## Method/Design

The proposed research is an experimental randomized controlled trial, risk prevention targeted. The study is divided into four sub-studies depending on the studied moderator: limiting bonuses, self-exclusion, self-limitation and information.

### Ethical approval

The participants were informed about the research and gave their written informed consent prior to their inclusion in the study. This study was approved by the French Research Ethics Committee (CPP) on January 8, 2013.

### Common methodology to all sub-studies

Media announcements (newspapers, radio, and websites) are used to recruit participants. In addition, we have subcontracted recruitment to survey institutes to obtain lists of potential participants. Recruitment began in March 2013 and will end in March 2017. Volunteers are asked to contact the research team by email, to obtain details of the study and arrange a telephone appointment to complete the pre-selection questionnaire. Inclusion criteria are: age 18 or older, currently gambling at least once during the past month on a website authorized by ARJEL, agreeing to give access to the gambling-account data and to be filmed during the experimental session. Exclusion criteria are: scoring 8 or more on the Canadian Problem Gambling Index (CPGI) [14], being actually under treatment for a gambling problem, being indebted, using psychoactive substances on the day of the experiment, participating in another clinical study during the week preceding the experiment, being pregnant, being under protection (guardianship or curatorship), having an history of psychosis or cognitive impairment, having a betting limit of less than 200 € - for the sub-study “limiting bonuses” (in order to allow randomization under any experimental condition) .

If they meet the eligibility criteria, and after providing informed consent, participants will have an interview prior to the experiment, to collect the following informations: sociodemographic data, gambling history and current gambling behavior, severity of cognitive distortions based on the Gambling Related Cognitions Scale (GRCS) [15], severity of gambling problems based on the CPGI [14], mood based on the Brief Mood Inspection Scale (BMIS) [16], feelings of loss of control, intensity of craving based on the Gambling Craving Scale (GACS) [17], gambling-account information and knowledge and use of online gambling protections.

The participants are then randomly assigned to one experimental condition in one sub-study. Randomization is conducted according to two characteristics of each gambler: favorite game (games of chance without skill, semi-skilled games of chance, and skilled games) and gambler status (problem or non-problem). Each new participant included is randomized between the different experimental conditions and the control condition, based on these two characteristics in order to dispatch the gamblers among all the possibilities with equal number of gamblers having preference in each of the three major forms of games and equal number of problem or non-problem gamblers in each experimental condition. The number of participants to be included was computed according to the number of experimental conditions in each sub-study. In absence of anterior results, reliable power calculation and sample size determination are not possible. Thirty participants are assigned to each experimental condition and 30*√(k) are assigned to the control group of each sub-study (k being the number of experimental conditions in the sub-study) in order to optimize the comparison between each condition and the control group [18]. Consequently, each experimental condition and control groups is composed of an equal number of gamblers chosen among 6 possibilities crossing the three forms of game (games of chance without skill, semi-skilled games of chance, and skilled games) and the two possible gambling status (problem gambler or non-problem gambler). The final sample will consist of 485 volunteers (Fig. 1).

**Fig. 1 Fig1:**
[figure not shown]
Study design

### Sub-study 1 “limiting bonuses”

The objective is to measure the effectiveness of limiting bonuses (currently nonexistent) and estimate the level of limitation for maximum efficiency. Efficiency will be measured according to the type of gambling and gambler status (problematic or not). A total of 180 participants will be recruited and randomized between the four proposed bonus amounts (€ 10 - n = 30, € 50 - n = 30, € 100 - n = 30, € 200 - n = 30) and the control group (n = 60), taking into account their game of choice and their gambling status.

The experimental session is a gambling situation on a computer at our research center. The gambler is invited to play on his favorite gambling site as usual, using his own gambling account and his own money. The participant is asked not to re-credit the account with any gains made during the experimental session (to avoid biasing measurement of the financial balance at the end of the gambling session). The presence of a camera will verify that the volunteer has not credited his in-game earnings (only the screen will be filmed). The gambling session ends when the participant wishes, but the session can last up to 4 h. The bonus given to the gambler is directly usable with a pre-paid card. It is given to the participant in the middle of the gambling session, to assess gambling behavior before and after obtaining the bonus.

An immediate post-test will be conducted at the end of the gambling session to collect the experimental data (Table 1).

**Table 1 Tab1:** Data collected in the post-test for all the studies

Post-test	Measurements
Interview	Enjoyment during the gambling session
	Feeling out of control during the gambling session
	Moderator impact on gambling practice
	Interest of this moderator for themselves and/or for problem gamblers
	Look at the gambling operator who proposes this measure
Statement of gambling parameters	Balance of the gambler’s account during the game session (or since the last visit)
	Number of bets during the game session (or since the last visit)
	Money earned during the game session (or since the last visit)
	Gambling time during the game session (or since the last visit)
	Compliance by the participants with game predictions (ie amount of money or time that the gambler planned to spend in gambling before the game session)
Questionnaires	BMIS (mood assessment) [16]
	GRCS (cognitive distortions assessment) [15]
	CPGI (gambling problems assessment) [14]
	GACS (intensity of craving assessment) [17]

### Sub-study 2 “self-exclusion”

The objective is to measure the effectiveness of self-exclusion as a moderator of gambling practice. This will be assessed 15 days and 2 months after the self-exclusion procedure. This study includes only problem gamblers. In fact, this protection is not intended for non-problematic gamblers who control their practice.

In all, sixty participants will be recruited for this sub-study and will be randomly assigned to the control group (n = 30) or the experimental group (n = 30). To be included in the experimental group, the gambler must implement the measure of self-exclusion necessarily offered by gambling operators approved by ARJEL. The self-exclusion is performed via a pre-test with the help of the evaluator, and concerns only the site of their choice. The player is excluded for the next 7 days and has the choice, at the end of this period, to extend the ban or not.

A post-test interview is conducted by phone 15 days after the establishment of self-exclusion and another one 2 months later for the same purpose (Table 1).

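### Sub-study 2 makes membership of the self-exclusion arm depend on carrying out the self-exclusion, with no matching condition for controls; read literally, this would compare implementers with unselected controls.

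*Protocol article*

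**What the plan says.** All statements are in the protocol article, under Method/Design.

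- **Order of steps (Common methodology to all sub-studies).** Eligibility, consent and a baseline interview come first: "If they meet the eligibility criteria, and after providing informed consent, participants will have an interview prior to the experiment". Allocation follows: "The participants are then randomly assigned to one experimental condition in one sub-study".
- **Allocation (Sub-study 2, self-exclusion).** Only problem gamblers are taken. "In all, sixty participants will be recruited for this sub-study", and they "will be randomly assigned to the control group (n = 30) or the experimental group (n = 30").
- **Condition on one arm (same section, next sentence).** "To be included in the experimental group, the gambler must implement the measure of self-exclusion". No such condition is placed on the control group.
- **How the act is done (same section).** "The self-exclusion is performed via a pre-test with the help of the evaluator, and concerns only the site of their choice".
- **Follow-up (same section).** "A post-test interview is conducted by phone 15 days after the establishment of self-exclusion and another one 2 months later".
- **Eligibility list (Common methodology).** It contains no criterion on willingness to self-exclude. It does contain one of this kind for sub-study 1: gamblers whose betting limit is under €200 are excluded so that any of the bonus conditions can be allocated to everyone randomised. The Discussion repeats that reason.

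**The concern.** In a randomised comparison, the allocation alone should decide who belongs to which arm. Here, belonging to the experimental arm also depends on something the participant does, and controls face no equivalent test. If some of those assigned to self-exclusion decline and the sentence is applied as printed, the experimental arm consists of implementers. The control arm still contains the people who would have declined.

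Willingness to lock one's own account may well be related to motivation to cut down or to gambling intensity, and so to the outcomes, which are money wagered and time spent gambling. The two arms would then differ for reasons other than self-exclusion. This is the article's only randomised contrast on self-exclusion, one of the four moderators named in the main objective, and the results are meant to inform policy. If decliners are never followed up, no analysis can restore the comparison.

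**Working it through.** **1. The plan's own figure.** The stated rule is 30 per experimental condition and 30√k controls, with k experimental conditions. Rounding the control group up, N = 30k + ⌈30√k⌉:

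- k = 1 (self-exclusion): 30 + 30 = 60
- k = 4 (bonuses): 120 + 60 = 180
- k = 3 (self-limitation): 90 + 52 = 142
- k = 2 (information): 60 + 43 = 103
- Sum: 60 + 180 + 142 + 103 = 485

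All agree with the article. The point is about design, not arithmetic.

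**2. Does the timing matter?** The reference to a pre-test leaves the exact moment of self-exclusion unclear.

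- If the act comes after allocation, the condition can remove people from one arm only.
- If it comes before allocation, the gambler's own choice would decide the group, which contradicts the 30:30 random assignment.

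Neither order reconciles the condition with random allocation.

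**3. Does anything beyond the one sentence support the literal reading?** Two things do.

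- Follow-up starts at the establishment of self-exclusion. A gambler who was assigned to it and declined has no such date, so the printed schedule gives no post-test for that person.
- Sub-study 1 puts its equivalent requirement before randomisation and applies it to all arms. Sub-study 2 puts it inside one arm.

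**4. Illustration on the ratio scale.** Let r be the share who would refuse and m the refusers' mean gambling relative to implementers (implementers = 1). Both are assumptions; the article gives neither. With no true effect:

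- experimental group (implementers only): mean = 1
- control group (unselected): mean = (1 − r) + rm = 1 + r(m − 1)
- apparent reduction = r(m − 1) / [1 + r(m − 1)]

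| r | m | Calculation | Apparent reduction |
|---|---|---|---|
| 10% | 1.5 | 0.05/1.05 | 5% |
| 20% | 2 | 0.20/1.20 | 17% |
| 20% | 3 | 0.40/1.40 | 29% |
| 30% | 3 | 0.60/1.60 | 38% |

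If m = 1 the result is zero. If m < 1 the sign reverses: with r = 20% and m = 0.5 the control mean is 1 − 0.10 = 0.90, and the experimental group appears to gamble 1/0.90 − 1 = 11% more.

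**5. Second illustration, on the standardised scale.** Suppose willingness is a normal latent variable with correlation ρ to the outcome (assumed). With the least willing share r removed from one arm, bias = ρ·φ(z_r)/(1 − r) in SD units. With 30 per arm, unit SD in both and a two-sided 5% test, the standard error is √(2/30) = 0.258.

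| Refusal | Bias, ρ = 0.3 to 0.5 | False-positive rate |
|---|---|---|
| 10% | 0.058 to 0.097 SD | 5.6% to 6.6% |
| 20% | 0.105 to 0.175 SD | 6.9% to 10.4% |
| 30% | 0.149 to 0.248 SD | 8.9% to 16.1% |

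At ρ = 0 the rate stays at 5%.

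**6. Effect on numbers.** To fill 30 places with implementers, 30/(1 − r) would have to be randomised to that arm: 34, 38 or 43 at 10%, 20% or 30% refusal, rounding up. Without replacement the arm would fall to 27, 24 or 21.

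**The case against.** A reader might infer that refusers are dropped and replaced until 30 implementers are reached, that randomisation is therefore broken, and that the comparison must favour self-exclusion. The article does not support that much.

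- **Removal is not stated.** Nothing says that a participant who declines is removed, replaced or left out of the analysis. The sentence may be a loose description of the intervention, since the next ones describe the procedure. This stands, and it limits the point to what the sentence implies if followed.
- **Analysis-set rules may be elsewhere.** A condensed article commonly leaves these to the full protocol or SAP, so their absence is no fault. This also stands. What can be charged is a stated arm-specific condition, which would conflict with an intention-to-treat rule if one exists.
- **Refusal may be rare.** Consent precedes allocation and an evaluator helps with the set-up. If the information given covered possible self-exclusion, both arms may already consist of people who accepted it. The article does not show this, but frequent refusal cannot be presumed.
- **The Background remark on low uptake does not help.** It concerns self-limitation in Internet sports betting, which is a different tool in everyday use. It gives no basis for a refusal rate here.
- **The direction is open.** More heavily involved or more distressed gamblers could be the more willing to self-exclude, so m could be below 1. Exclusion at a CPGI score of 8 or more also narrows the range of severity, which makes a value such as m = 3 harder to assume.

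**Conclusion.** The concern holds as a fault in a stated rule. Sub-study 2 sets an inclusion condition on one randomised arm that depends on the participant's own act, starts follow-up from that act, and has no matching criterion before randomisation. Followed as written, it would compare implementers with unselected controls. Bias arises only if some of those assigned decline and declining is related to gambling behaviour. The article fixes neither, so every figure above is illustrative, and the 38% in particular rests on the most extreme pair of assumptions used.

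The claim that randomisation is in fact broken in favour of self-exclusion goes beyond the text. The scope is 60 of 485 participants. Should-fix, moderate confidence.

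**What to change.** 1. Delete the sentence that makes inclusion in the experimental group depend on implementing self-exclusion.
2. Add an inclusion criterion for both arms of sub-study 2, checked before randomisation: the gambler is willing to activate the 7-day self-exclusion on the chosen site if assigned to it. This follows the approach already taken for the betting limit in sub-study 1.
3. Time the follow-up interviews from randomisation in both arms.
4. State that all 60 are kept, followed and analysed in the arm assigned, and that those who decline are not replaced.
5. Report the share of the experimental arm who activated the exclusion.

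The sample size stays at 60. The cost is a slightly narrower population (gamblers willing to self-exclude) and some dilution of the effect from those who do not activate. If the full protocol already keeps everyone as randomised, only the conflicting sentence and the follow-up clock need correcting, and the willingness criterion remains advisable.
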